### Detailed procedure

The researcher will screen the candidate for a lung nodule excision procedure for suspected lung cancer. All the patients screened for suspected lung cancer and evaluated for lobectomy are studied in the preoperative period and undergo a total body CT scan, PET scan, and respiratory function tests as suggested in European and International guidelines (in addition, shuttle test and cardiopulmonary function test are performed if deemed necessary according to the respiratory function tests) and chest or brain MRI if needed for further clinical necessities. The patient’s clinical history, vital signs, clinical exams, blood tests, and radiological exams will be examined to assess inclusion and exclusion criteria. The patient signs the written informed consent during the screening visit and is enrolled in the study. The pregnancy test will be performed 1 to 2 days before the infusion of the study drug.

The drug infusion will be performed 2 to 5 days before the surgery: the patients will receive 100 mg of cetuximab intravenously over 30 min to differentiate between an infusion reaction to the unlabeled cetuximab and a cetuximab-IRDye800 reaction and to preload the hepatic EGFR, and a dose of 50 mg of cetuximab-IRDye800 over 30 min to 1 h [3]. The doses were determined based on previous findings by other authors, showing that 25 mg/m2 provided the optimal tumor-to-background ratio. EKGs (electrocardiograms) will be performed at screening, 30 min post-infusion of the unlabeled cetuximab loading dose, two h post-infusion of the cetuximab-IRDye800, and follow-up on day 30. After the drug infusion phase, patients will undergo VAT resections of the lung nodule (between days 2 and 5 post-infusion). During post-surgery hospital stays and after discharge to home, patients will be treated and followed up according to clinical practice.

Patients will be monitored for toxicity and compliance with a clinical assessment after discharge. Moreover, subjects will be instructed before participation on the importance of reporting any symptoms (new or worsening), and/or any physical changes throughout their participation in the study. Morbidity or toxicity will be assessed during and after drug infusion, during and after a hospital stay, and during and after the control visits. If subjects discontinue before study completion, they will be encouraged to return for safety evaluations.

Study drug will be discontinued for any of the following: Subject withdraws consent for the study, death attributed to study drug, serious systemic anaphylactic reaction (grade 3), or any serious rare reactions attributed to study drug.

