## Methods

### Materials and equipment

We included patients diagnosed with NSCLC in clinical stage I (according to 8th Edition of TNM Staging System) who have been considered candidates for minimally invasive surgical resection after pre-operative assessment, including chest CT scans, PET, and respiratory function tests.

Regarding the age, we included patients ranging from 18 to 80. Patients with adequate bone marrow, kidney, liver, and heart function were included in the study. The included patients must have a PS ≤ 2, and potentially fertile female subjects must agree to use highly effective contraception throughout the study and for three months after the last dose of the study medication (According to CTFG recommendations related to contraception and pregnancy testing in clinical trials - Version 1.1–2020). The patients excluded from the study presented with characteristics like previous systemic treatments (chemotherapy, immunotherapy) for lung cancer, prior radiotherapy on lung or mediastinum, concomitant disorders that compromise the ability to adhere to the procedures of the protocol, Hb levels < 9 gm/dL, platelet count < 100,000/mm3, leukocyte count < 3000/mm3, absolute neutrophil count < 1500/mm3, electrolytes lower than the lower limit of normal per institution average lab values, TSH < 13 micro international units/mL, administration of an investigational drug within 30 days before the first dose of cetuximab IRDye800, MI, UA, heart failure, stroke or liver failure within 6 months before enrollment, previous infusional reactions to cetuximab or other monoclonal antibody therapies, evidence of QT prolongation, current therapy with antiarrhythmic agents including quinidine, procainamide, dofetilide, amiodarone, sotalol. Both pregnancy and present breastfeeding were considered exclusion criteria.

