The study’s primary outcome is focused on the proportion of patients with lung nodules detected during surgery by NIR camera. The objective is to evaluate if cetuximab-IRDye800 can make visible lung nodules to the NIR camera through surgical procedures. The NIR camera used will be the EleVision™-Iridium VS3 (Medtronic, Dublin, Ireland). The detection of lung nodule NIR emission is registered in the first 5 min of the NIR camera activation during the surgery. The nature of the identified nodules (neoplastic or not) will be recorded during the surgery (sending the resected specimen for intraoperative pathology report (i.e., frozen section), later confirmed by the definitive pathology report) or 20–30 days after surgery according to the standard procedures in our center for the pathologic analysis of the operative specimens.

The secondary outcomes include a broad spectrum of items: the proportion of patients with unexpected cancer localization detected during surgery by NIR camera, the proportion of patients with negative surgical margins, the evaluation of the time spawns between the insertion of the NIR camera and the visualization of the nodule; and the possible morbidity of the drug assessed during and after the drug infusion.

The data will be collected from patient’s clinical records, entered in a secured password-locked web application, and then organized in a second password-locked database for easier data management. The data will include, at each relevant time point (Table 1), patient identification and anonymous demographic data, comorbidities, concomitant medications, vital signs, height and weight, Performance Status, adverse events (date of onset and resolution, maximum grade, relation to the study drugs), laboratory results, target, and non-target lesions assessments (dates and results), pulmonary function test, surgical details, post-operative data (complications, pain evaluate by NRS scale system, hospital length of stay) and final pathological staging. After the end of the protocol treatment, patients will be followed according to clinical practice (i.e. outpatient clinic follow-up visit with thorax and abdomen CT scans).

The expected rate of subjects lost to follow-up after surgery for early-stage lung cancer (as documented by large randomized clinical trials in this setting) is likely less than 5% and should not invalidate trial results. The data obtained during the trial will be treated under the applicable national and EU regulations.

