
Demographic and baseline characteristics will be presented for all patients. Discrete data will be summarized by frequencies and percentages. Continuous variables will be summarized using standard measures of central tendency and dispersion (mean and standard deviation or median and interquartile range).

The efficacy and safety analysis will be conducted on all patients undergoing surgery with cetuximab-IRDye800. A Hern’s Single-Stage Phase II design will be used. The study sample size has been calculated according to the efficacy endpoint. The efficacy analysis will be performed after the enrolment of 25 patients. The efficacy analysis will estimate the proportion of lung nodules correctly visualized by the NIR camera during surgery, with 90% confidence intervals (according to the 1-sided alpha error of 0.05). It is expected that cetuximab-IRDye800 will improve the proportion of NSCLC nodules detected intraoperatively from 40% (obtained employing white camera visualization) [7] to 70% by adding cetuximab-IRDye800. To conclude that the cetuximabIRDye800 is promising, the null hypothesis will be rejected if 15 or more patients out of 25 patients are correctly identified intraoperatively.

Toxicity will be recorded and classified according to the definitions of the NCI criteria “Common Terminology Criteria for Adverse Events (CTCAE),” version 5.0.

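### Patients with benign nodules can enter the 25-patient denominator of a test whose 40% and 70% are rates for NSCLC nodules, and the article does not say how they count

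*Protocol article*

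**What the plan says.** All references are to the protocol article.

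- **Eligibility (Materials and equipment).** "We included patients diagnosed with NSCLC in clinical stage I". The pre-operative assessment named there is chest CT, PET and respiratory function tests.
- **Entry (Detailed procedure).** "The researcher will screen the candidate for a lung nodule excision procedure for suspected lung cancer". Criteria are then checked on clinical history, vital signs, clinical and blood tests and imaging, and the patient consents and is enrolled at the screening visit. Biopsy or histology is not listed.
- **Pathology (Materials and equipment).** "The nature of the identified nodules (neoplastic or not) will be recorded during the surgery", by frozen section later confirmed by the definitive report, or 20–30 days after surgery.
- **Hypothesis (Materials and equipment).** The tracer is expected to "improve the proportion of NSCLC nodules detected intraoperatively from 40% (obtained employing white camera visualization) [7] to 70% by adding cetuximab-IRDye800".
- **Design and analysis (Materials and equipment).** "A Hern’s Single-Stage Phase II design will be used", and the proportion is to be estimated "with 90% confidence intervals (according to the 1-sided alpha error of 0.05"). "The efficacy analysis will be performed after the enrolment of 25 patients". The null is rejected if at least 15 of the 25 are correctly identified. The efficacy set is all patients operated on with the tracer, with no restriction to confirmed NSCLC.

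**The concern.** The hypothesis is about NSCLC nodules, but the analysis set is defined by having had the operation. The two coincide only if NSCLC is established before entry, and the article is not consistent on whether it is.

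If a patient with a benign nodule is among the 25, the article gives no rule for counting that patient. The primary outcome is worded as nodules detected, without reference to pathology. The statistical paragraph speaks of nodules visualized, and patients identified, *correctly*, but does not define the word. Two readings are open:

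- A benign nodule that stays dark, which is the desired behaviour of a tumour-specific tracer, is a failure because the patient remains in the denominator.
- A benign nodule that fluoresces is a success because a nodule was detected.

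Under the first, a tracer that performs as planned in cancer can miss the threshold. Under the second, non-specific fluorescence helps to reach it. Either way the primary proportion would mix detection of NSCLC with the benign share of the enrolled patients.

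**Working it through.** **Inputs from the article:** n = 25; success if X ≥ 15; p0 = 0.40; p1 = 0.70; one-sided alpha 0.05.

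**Assumptions, because the article gives neither figure:** b, the number of benign-nodule patients among the 25; and q, the probability that a benign nodule is recorded as detected and counted as a success.

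**Step 1. The plan's own rule, all 25 NSCLC (exact binomial).**
- Alpha = P(X ≥ 15 | 25, 0.40) = 0.0344.
- Power = P(X ≥ 15 | 25, 0.70) = 0.9022.
- A cutoff of 14 would give alpha 0.0778, so 15 is the correct cutoff at 0.05. 25 with cutoff 15 is also the smallest single-stage design with power of at least 90%. The rule is sound for 25 NSCLC patients. The power is implied; the article does not state it.

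**Step 2. Benign patients in the denominator, NSCLC detection at 70%.** The number of successes is Bin(25 − b, 0.70) + Bin(b, q), and power is the probability that the sum is at least 15.

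| b | q = 0 | q = 0.4 | q = 0.7 |
|---|---|---|---|
| 0 | 0.902 | 0.902 | 0.902 |
| 1 | 0.847 | 0.879 | 0.902 |
| 2 | 0.771 | 0.851 | 0.902 |
| 3 | 0.671 | 0.820 | 0.902 |
| 4 | 0.551 | 0.784 | 0.902 |
| 5 | 0.416 | 0.744 | 0.902 |

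At q = 0.7 nothing is lost, but only because the tracer then does not distinguish benign from malignant nodules.

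**Step 3. The other direction, NSCLC detection at only 40%.** With b = 5 and q = 0.7, P[Bin(20, 0.40) + Bin(5, 0.70) ≥ 15] = 0.1075 (0.10747 unrounded, so 10.7%), against 0.0344 with no benign patients. With b = 5 and q = 0 the same probability is 0.0016. Steps 2 and 3 are therefore not harms that add up: power is lost when q is below 0.7, and false success rises above the planned 3.4% when q is above 0.4. The large losses in Step 2 and the 10.7% come from different values of q.

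**Step 4. Confirmed NSCLC only.** For m evaluable patients, take the smallest r with P(X ≥ r | m, 0.40) ≤ 0.05.

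| m | cutoff r | alpha | power at 0.70 |
|---|---|---|---|
| 25 | 15 | 0.034 | 0.902 |
| 24 | 15 | 0.022 | 0.847 |
| 23 | 14 | 0.035 | 0.880 |
| 22 | 14 | 0.022 | 0.814 |
| 21 | 13 | 0.035 | 0.852 |
| 20 | 13 | 0.021 | 0.772 |

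At m = 22 this gives 81%, against 67% if three dark benign nodules stay in the denominator under a fixed cutoff of 15. At m = 24 the cutoff is still 15, so power is 85% either way.

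**The case against.** The strongest defence is that suspicion is not a second eligibility criterion. The Detailed procedure section describes the pool being screened and then refers to the inclusion and exclusion criteria, which lead back to diagnosed NSCLC. If that criterion is enforced with pre-operative histology, no benign nodule enters and Step 1 stands unchanged. Pathology after resection proves nothing, since specimens are examined in any case. This stands in part. A reader might infer that benign nodules will be in the 25 and that the 90% power is lost; the article supports only that they can be and that it can be. But the data listed for checking eligibility omit histology, and the Background presents the tracer as part of a diagnostic as well as a therapeutic procedure for indeterminate nodules, so the gap is real.

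A reader might also infer that a fluorescing benign nodule is certain to count as a success. The article does not show that. Requiring correct identification, together with recording whether a nodule is neoplastic, could be meant to exclude it. What can be said is that the term is undefined.

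Finally, an all-operated primary set is a legitimate choice. It would then need p0 and p1 set for a mixed population, whereas the article's rates are for NSCLC nodules.

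**Conclusion.** The point holds as a mismatch between population, hypothesis and analysis set, with a conditional consequence. The article is inconsistent on whether NSCLC must be established before entry, tests rates for NSCLC nodules in all operated patients, and leaves open how a benign nodule counts.

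The cutoff itself is correct for 25 NSCLC patients. The size of the problem rests on two quantities the article does not give. With 3 benign patients, power is 67%, 82% or 90% at q = 0, 0.4 or 0.7; with 5 it is 42%, 74% or 90%. At q = 0.7 with 5 benign patients, the probability of declaring an inadequate tracer promising is 10.7%. If histology is required and enforced before entry, the effect is nil. With so small a sample the denominator should be settled before results are seen, because one or two patients matter: two dark benign nodules take power from 90% to 77%.

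**What to change.** 1. Reconcile the eligibility paragraph with the Detailed procedure section: state whether histological NSCLC is required before entry.
2. Define the primary efficacy set as operated patients whose index nodule is NSCLC on definitive pathology, and define correct identification as NIR detection of that nodule.
3. Apply the exact cutoff for the number attained: 15 of 25, 15 of 24, 14 of 23, 14 of 22, 13 of 21, 13 of 20.
4. Report NIR positivity in benign nodules separately, and keep the all-operated analysis as a sensitivity analysis.

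The change is to wording; the pathology is already collected. The primary result would wait 20–30 days for the definitive report. Power is not held at 90%: it is 85%, 88%, 81%, 85% and 77% at 24, 23, 22, 21 and 20 evaluable patients, and this should be stated. If the sponsor wants to keep 90%, the alternative is to enrol until 25 are confirmed, at 25/(1 − f) patients for a benign share f: 25/0.9 = 27.8, so 28, at 10%, and 25/0.8 = 31.25, so 32, at 20% (both shares are assumptions).

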## Discussion

### Expected results

We hypothesize that using cetuximabIRDye800 during minimally invasive surgical procedures for lung cancer could overcome the limitation demonstrated by ICG and the traditional localization strategies (e.g., coil, hook, dye intra-tumoral injection). We expect to validate the use of an optimal tracker that can be easily applied intraoperatively during minimally invasive lung surgical procedures, to define the optimal time window and the optimal dose of administration of the tracker, and to discover neoplastic localization in lymph nodes and lung parenchyma not predictable pre-operatively. In this sense, application in surgically treated pancreatic cancer and cancer Head and Neck has shown encouraging results [21, 22]. We performed the synthesis of the NIR tracker to verify the values of excitation/emission. Moreover, other groups have already published pre-clinical studies on the efficacy of anti-EGFR antibodies conjugated with NIR-Dye (including IRDye^®^ 800CW) in detecting lung cancer in both in-vitro and in-vivo settings [23]. Finally, several phase I-II clinical trials demonstrated that the cetuximab-IRDye800 could be safely administered to humans and that the adverse events of the labeled antibody (cetuximab-IRDye800) were consistent with the known toxicity profile of unlabeled cetuximab [24].

#### Ethics

As far as the ethics are concerned, cetuximab-IRDye800 was evaluated by several phases I-II clinical trials that demonstrated that it could be safely administered to humans and that its adverse events were consistent with the known toxicity profile of unlabeled cetuximab 24. All other exams and procedures are routine practice except for the control EKG (electrocardiogram) after and during study drug infusion. No major ethical concerns are present. The study will be covered by ad-hoc institutional insurance. All pre-clinical and clinical studies showed that the structure and the capability of the antibody to bind to EGFR, the clinical pharmacology, the clinical pharmacokinetic, and the clinical toxicology of cetuximab-800CW is therefore expected to be similar to that of unconjugated cetuximab. Moreover, since the total tracer dose (up to 50 mg flat dose) is much lower than doses given during the regular clinical application of cetuximab (up to 400 mg/m2, which translates to 680 mg for an average person), risks related to the drug infusion may be reduced in respect of the routine practice of cetuximab therapy. Moreover, if the drug infusion is successful in identifying lung nodules, lymph-nodal metastasis, or unexpected cancer localization (even just one of these outcomes), the patients enrolled in the study could benefit from more radical surgical procedure and a better cancer staging and consequently more adequate post-operative complementary therapy, that if submitted to the standard of care.

All authors have read and agreed to the published version of the manuscript.

## Data Availability

Data is provided within the manuscript.
